### Primary outcome measures

Surgical site infection will be our primary outcome - the assessment for any evidence of surgical site infection will be done 72 hours after caesarian section, as well as on follow-up days (Day 7 and Day 30 post-caesarean section). Two clinicians in the ward who are not aware of the study group allocation will perform diagnosis of surgical site infection. The presence of fever (febrile morbidity), signs and symptoms of abdominal wound infection or endometritis will indicate surgical site infection. Febrile morbidity will be defined by temperature above 38°C at least 4 hours apart on two or more occasions, excluding the first 24 hours after delivery [33]. Abdominal wound infection will be defined by partial or total dehiscence or presence of purulent or serous discharge from the wound with indurations, warmth and tenderness.

Endometritis will be defined by the presence of fever (38°C or above) in association with one or more of the following: uterine tenderness or foul smelling lochia [33]. In both groups, the bladder catheter will be removed after 24 hours. Wound care will follow the standard scheme in both groups, the occlusive dressing applied in the theatre and removed after 48 hours. The patient will be discharged on Day 3 if there is no sign of infection or complication and asked to return on Day 7 in order to have her stitches removed. Then, the patient will return on Day 30 post-caesarean section for reassessment. On Day 7 and Day 30, axillary temperature will be measured, and the abdomen and wound will be examined for signs of infection and sutures will be removed on the first follow-up visit.

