### Sample size estimation

The incidence of surgical site infection ranges between 2.5% and 20%. Zelenitsky *et al.*, in his prospective randomized study, found that deep surgical site infection rates were 8.1% and 6.9% in the single high dose and multiple standard dose groups, respectively [31].

For the purpose of this study, which involves candidates who undergo emergency or non-elective caesarean section, we use Ps = 8.1%, which is the proportion of participants in the single dose antibiotic prophylaxis group expected to develop surgical site infection post caesarian section, and Pn = 6.9%, which is proportion of participants in the multiple dose antibiotic prophylaxis expected to develop surgical site infection. If we assume the hypothesized difference, D to be 5%, the sample size needed to reject this hypothesis at alpha = 0.05 and beta = 0.20 is [32]:

(1)$${\left({\text{Z}}_{0.95}\;\text{+}\;{\text{Z}}_{0.80}\right)}^{2}\;\left[\text{Ps}\left(1-\text{Ps}\right)\text{Pn}\;+\left(1-\text{Pn}\right)\right]/{\left(\text{Ps-Pn-D}\right)}^{2}$$

Substituting to the formula, the total required sample size: 444 (that is, the required sample size in each group will be 222).

When considering 10% of participants drop out or are lost to follow-up, the required sample size will be 490; that is, each group will contain 245 participants.

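### Fever alone counts as surgical site infection, while the trial is sized on deep-infection rates, so the stated 80% power does not refer to the outcome analysed

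*Protocol article*

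**What the plan says.** **Outcome.** Under Primary outcome measures, the rule is "The presence of fever (febrile morbidity), signs and symptoms of abdominal wound infection or endometritis will indicate surgical site infection". The three parts are alternatives, so any one is enough. The fever part rests on temperature and timing alone: "Febrile morbidity will be defined by temperature above 38°C at least 4 hours apart on two or more occasions", with the first 24 hours after delivery left out. Endometritis has its own definition in the same section: a temperature of 38°C or above, with uterine tenderness or foul lochia, and no repeat reading. Wound infection is defined by local signs. For the later visits the text says: "On Day 7 and Day 30, axillary temperature will be measured, and the abdomen and wound will be examined for signs of infection". The next section states that there are no secondary outcomes.

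**Planning rates.** Under Sample size estimation, a cited randomised study "found that deep surgical site infection rates were 8.1% and 6.9% in the single high dose and multiple standard dose groups, respectively". These figures become the expected rates here: "we use Ps = 8.1%, which is the proportion of participants in the single dose antibiotic prophylaxis group" and "Pn = 6.9%, which is proportion of participants in the multiple dose antibiotic prophylaxis expected to develop surgical site infection". The difference to be ruled out is set by "If we assume the hypothesized difference, D to be 5" percentage points, with alpha 0.05 and beta 0.20. The result is 222 per group, raised to 245 for dropout.

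**Analysis.** Under Data analysis, the effect measure is the absolute difference in proportions. A relative ratio is presented as well.

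**The concern.** Fever with a uterine sign already counts as endometritis, and wound infection has its own criteria. What the fever part adds is women with raised temperatures and neither kind of local sign. No other cause of fever has to be excluded. Two things follow.

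- The outcome is wider than deep infection. It takes in endometritis, serous wound discharge with local signs, and isolated fever. The planning rates also come from a comparison of a single high dose with multiple standard doses, whereas both arms here start with the same dose. A power figure built on those rates describes a different outcome.
- If some isolated fever has nothing to do with the regimen, it adds events to both arms. That brings the arms closer together, most visibly on the ratio scale, and raises the variance. The study hypothesis is that the regimens do not differ by a clinically significant amount, so a wrong power figure and a noisier outcome both bear on how the result can be read.

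Two smaller points belong with this. The section uses two fever cut-offs, and it does not say how the two-reading rule is to be applied on Day 7 and Day 30.

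**Working it through.** **Inputs from the document.** Ps = 0.081, Pn = 0.069, D = 0.05, one-sided z of 1.645 (the formula uses Z at 0.95), z of 0.842 for 80% power, and 222 per group.

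**Input assumed.** f is the proportion of otherwise uninfected women with isolated fever unrelated to regimen, equal in both arms. The documents give no value. The range 2%, 5%, 10% is for illustration.

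**Step 1: the plan's own figure.** The plus sign in the printed bracket is misplaced. With the usual variance,

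n = (1.645 + 0.842)² × [Ps(1−Ps) + Pn(1−Pn)] / (Ps − Pn − D)²

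The squared sum is 6.183 and the bracket is 0.1387.

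- With the printed denominator, (0.081 − 0.069 − 0.05)² = 0.038², n = 593.8, so 594 per group.
- With the sign of Ps − Pn reversed, the denominator is 0.062² and n = 223.0, close to the stated 222.

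The stated size therefore depends on a sign reversal. That is a separate error. Power is shown below both ways so that the effect of the outcome definition can be seen apart from it.

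**Step 2: rates for the composite.** Each rate p becomes p + f(1 − p), so any difference between arms is multiplied by (1 − f).

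**Step 3: power at 222 per group.** SE = √{[Ps(1−Ps) + Pn(1−Pn)]/222}, using the composite rates. Power = Φ[(D − (Ps − Pn))/SE − 1.645] with the printed sign, and Φ[(D + (Ps − Pn))/SE − 1.645] on the protocol's arithmetic. At f = 0, SE = 0.0250. The two arguments are 0.038/0.0250 − 1.645 = −0.124, giving 45%, and 0.062/0.0250 − 1.645 = 0.836, giving 80%.

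| f | Rates, single / multiple | Power, protocol's arithmetic | Power, printed sign |
|---|---|---|---|
| 0 | 8.1% / 6.9% | 80% | 45% |
| 2% | 9.9% / 8.8% | 72% | 40% |
| 5% | 12.7% / 11.6% | 63% | 35% |
| 10% | 17.3% / 16.2% | 53% | 30% |

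**Step 4: a true excess equal to D.** Take 11.9% against 6.9%. The last column is the chance of wrongly ruling out a 5-point difference with 222 per group.

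| f | Observed difference | Observed ratio | Wrongly ruling out D |
|---|---|---|---|
| 0 | 5.0 points | 1.72 | 5.0% |
| 2% | 4.9 points | 1.56 | 5.4% |
| 5% | 4.75 points | 1.41 | 5.8% |
| 10% | 4.5 points | 1.28 | 6.6% |

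On the absolute scale the shrinkage is small. The ratio moves more. The main cost is the higher event rate, which raises the variance and lowers power.

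**Step 5: the fever rules side by side.** Febrile morbidity needs a temperature above 38°C, repeated. Endometritis needs 38°C or above, not repeated. A reading of exactly 38.0°C counts for one and not for the other. One reading at one visit cannot meet the repeat rule, and the text does not say whether readings are repeated at follow-up or may be combined across visits.

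**The case against.** A composite of fever, wound infection and endometritis is openly defined and is assessed by clinicians unaware of allocation. The hypothesis concerns post-caesarean infection in general. The fever part is already filtered: readings must be repeated, the first 24 hours are excluded, and women with fever or features of chorioamnionitis before surgery are not eligible. This stands as a defence of choosing the composite. It does not defend sizing the composite on deep-infection rates.

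A reader might infer that the fever rule cannot be met after discharge because each visit takes a single temperature. The text does not support this. It gives no number of readings, and high readings at two visits would literally be more than 4 hours apart. Fever with a uterine sign also still counts at follow-up, as endometritis. If the rule did go unmet after discharge, there would be fewer isolated-fever events and so less dilution.

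A reader might also infer that the definition dilutes any true difference. That requires the added fever to be unrelated to regimen, and the documents do not show this. Some isolated fever may be infection that the regimens affect, and then the direction of bias is not fixed. Nor does the noise act only in favour of finding no difference. In the test the trial is sized for, it mainly makes a 5-point difference harder to rule out.

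Finally, replacing the primary outcome of an open-label trial that is already recruiting carries its own risk. That objection stands and limits the remedy.

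**Conclusion.** The point holds in a limited form. Isolated fever is a primary event, and the planning rates belong to a narrower outcome. The stated 80% power is therefore not a property of the planned analysis. This conclusion needs no assumption about fever.

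The size does need one. With isolated fever unrelated to regimen in 2% to 10% of otherwise uninfected women in both arms, the loss is 8 to 27 percentage points of power on the protocol's own arithmetic (80 − 72 and 80 − 53), or 5 to 15 with the printed sign (45 − 40 and 45 − 30). The low starting value of 45% comes from the separate sample-size error and should not be attributed to the outcome definition. Bias on the absolute scale, the protocol's effect measure, is at most half a point over this range.

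The differing cut-offs and the silence on readings at Day 7 and Day 30 are matters of wording. They should be settled, but they do not themselves cause dilution.

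**What to change.** 1. Restate the power for the composite as defined, over a range of event rates instead of the deep-infection rates alone. About 7% to 20% would do: from near the lower planning rate to the upper end of the incidence range that the protocol cites.
2. Before any comparison by arm, pre-specify an analysis of wound infection or endometritis by the criteria already in Primary outcome measures, with isolated febrile morbidity reported separately. Make this the primary outcome only if the decision is taken blind to outcome by arm.
3. Reconcile the two fever cut-offs, and state how the two-reading rule applies on Day 7 and Day 30.

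**Cost.** The stated power will look less favourable. The narrower analysis will have fewer events. The case record form must record fever, wound signs and uterine signs as separate items. The article does not show whether it already does, so some added data collection may be needed.

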### Secondary outcome measure

There are no secondary outcome measures.

### Data collection

All data will be extracted from patients’ files and filled in a case record form designed for this study. Data to be collected will include the woman’s socio-demographic characteristics, obstetric history (past and present), and labor history if any (stage of labor, state of amniotic membrane-whether intact or ruptured) and others. Information on the HIV status of all women will also be collected. Patients’ information will be added during follow up.

### Data management

Data will be entered in Epi data 3.1 software (Epidata Association, Odense, Denmark) and later transferred into SPSS version 17.0 (University of Chicago, Chicago, USA) for analysis. Cleaning will be done using the same package.

### Data analysis

Analysis will involve baseline and hypothesis testing. Baseline analysis will involve comparing of the baseline characteristics between the two study arms. Hypothesis testing will be done to determine if there is a significant difference in cumulative incidence of post-caesarian infection between women under single dose antibiotic regimen and those under the multiple-doses antibiotic regimen. The analysis will be done as per protocol. The absolute difference in the proportion of women who will develop surgical site infection in the two study arms will be the effectiveness of one regimen over the other. Results will be presented in cumulative incidence and as a relative ratio together with 95% confidence intervals and *P*-value. Sub-group analysis will be performed by logistic regression to determine the association between surgical site infection and other covariates, such as HIV status, duration of operation, stage of labor and so on. Covariates with *P*-value less than 0.05 will be considered significant. Efforts will be made to trace by calling those who will be lost to follow so as to determine their well-being, this information will be incorporated into the data collection form (Additional file 1).

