### Study hypothesis

In this study, the hypothesis is: “there is no clinically significant difference between a single dose of gentamicin in combination with metronidazole and multiple doses over 24 hours for prevention of post caesarean infection".

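### The trial is sized to reject a 5-point excess, but the analysis plans a test for a significant difference and carries the 5 points into no decision rule

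*Protocol article*

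**What the plan says.** Three sections of the protocol article bear on the primary comparison.

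- **Study hypothesis:** "there is no clinically significant difference between a single dose of gentamicin in combination with metronidazole and multiple doses over 24 hours". Similarity is what the investigators expect to find.
- **Sample size estimation:** "If we assume the hypothesized difference, D to be 5%, the sample size needed to reject this hypothesis", at "alpha = 0.05 and beta = 0.20". The formula uses Z0.95 and has (Ps-Pn-D) squared in the denominator, with Ps = 8.1% (single dose) and Pn = 6.9% (multiple doses). It reports that "the required sample size in each group will be 222", raised to 245 per group for 10% dropout.
- **Data analysis:** "Hypothesis testing will be done to determine if there is a significant difference in cumulative incidence of post-caesarian infection". The absolute difference in proportions is named as the measure of effectiveness. Then: "Results will be presented in cumulative incidence and as a relative ratio together with 95% confidence intervals and" a P-value.

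D is not mentioned after the sample size section. The article does not use the terms non-inferiority or margin. No section compares a confidence limit with 5 points.

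**The concern.** The two sections test opposite nulls. In the sizing, the null is a 5-point difference, and rejecting it shows that the single dose is acceptable. In the analysis, the null is no difference, and rejecting it shows that the regimens differ. Under that second test, the only outcome that agrees with the study hypothesis is a failure to reject, and noise and a small sample make that outcome more likely.

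Surgical site infection is the only outcome, and the section on dissemination says that the findings will shape the hospital's prophylaxis protocol. The stated test does not control the error that matters for that decision: adopting a single dose that is in truth 5 points worse.

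**Working it through.** **Inputs** (Sample size estimation): Ps = 0.081, Pn = 0.069, D = 0.05, one-sided alpha 0.05 (Z = 1.645), power 80% (Z = 0.842), 222 per group before dropout and 245 after.

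**1. Which kind of formula gives 222?** The printed bracket has a misplaced plus sign. The usual form is

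n = (Z0.95 + Z0.80)² × [Ps(1-Ps) + Pn(1-Pn)] / (Ps-Pn-D)².

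- Variance term: 0.074439 + 0.064239 = 0.138678.
- Denominator from the stated rates: (0.012 - 0.05)² = 0.038².
- n = 6.1826 × 0.138678 / 0.001444 = 593.8, so 594 per group, not 222.
- With 0.062 (= 0.05 + 0.012, the sign of the expected difference reversed) in place of 0.038: 6.1826 × 0.138678 / 0.003844 = 223.0. With Z rounded to 1.64 and 0.84: 6.1504 × 0.138678 / 0.003844 = 221.9, which matches the stated 222.
- A two-sided 5% test for a difference needs 7,562 per group for 8.1% vs 6.9%, and 534 for 6.9% vs 11.9%. Neither is near 222.

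So the stated size comes from a margin-type formula with D = 5 points. That 222 does not follow from the stated rates is a separate fault, but it affects the figures below.

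**2. Single dose truly 5 points worse** (6.9% + 5 = 11.9% vs 6.9%). Exact binomial enumeration; pooled two-sided z-test at 5%; margin rule = upper Wald limit of the two-sided 90% CI for the risk difference below 0.05.

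| n per group | P>0.05 on the difference test | Wrongly passes the margin rule |
|---|---|---|
| 222 | 56.0% | 5.4% |
| 245 | 52.5% | 5.4% |
| 594 | 15.6% | 5.2% |

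The margin rule holds its error near 5% at every size. The rate of non-significant results depends strongly on n.

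**3. At the planning rates** (8.1% vs 6.9%), 222 per group: P>0.05 occurs in 92.5% of trials. In 47% of all trials P>0.05 while the upper limit of the 90% CI is still 5 points or more.

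**4. One possible result:** 24/222 vs 15/222. The difference is 4.1 points, P = 0.13, 95% CI -1.2 to 9.3 and upper 90% limit 8.5. It is not significant, yet an excess above 5 points is not excluded.

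**5. Power of a margin rule at the planning rates** (exact enumeration):

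| n per group | 90% CI rule | 95% CI rule |
|---|---|---|
| 222 | 46% | 34% |
| 245 | 49% | 37% |

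**The case against.** Several points on the other side have force.

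- **The absolute difference is already planned.** This stands. The Abstract and the Data analysis section both name it, on the same scale as D. What is missing is the threshold; the intervals are mentioned only in the sentence on presenting cumulative incidence and relative ratio.
- **The article never says that P>0.05 will count as proof of equal efficacy.** This also stands. A reader might infer that the investigators intend it, but no section says so, and the sample size section itself treats the 5-point difference as the hypothesis to reject. What can be said is that no other decision rule is given.
- **The design is never called non-inferiority.** True. The label is inferred from D, the one-sided Z and the denominator; step 1 supports it.
- **The 56% mixes two faults.** This stands. A reader might take the whole gap between 56% and 5% as the effect of the wrong test. At 594 per group the figure is 16%, so much of the gap comes from the small sample; the excess over 5% that remains is due to the test.
- **A 95% interval beside a one-sided 5% test is not in itself a contradiction.** Agreed. The interval is for presentation, and if used for the decision it would only be stricter. The article needs to say which interval decides.
- **An article condenses a fuller plan.** This does not answer the point: the Data analysis section states a test, and that test does not match the sizing.

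**Conclusion.** The concern holds in this form: the stated analysis cannot answer the question for which the trial was sized, because the 5-point D enters no decision rule. The mismatch can be read directly from the text and does not depend on an unseen analysis plan.

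Its size is that a true 5-point excess would go undetected in 56% of trials at 222 per group, or 53% at 245, against about 5% wrongly accepted under a margin rule. These figures assume a multiple-dose rate of 6.9%, a two-sided 5% pooled test and Wald limits. They describe the test and the sample size together. They do not show that the investigators will misreport a non-significant result.

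**What to change.** In the Data analysis section, make the primary analysis the risk difference, single minus multiple dose. Conclude non-inferiority only if the upper limit of the two-sided 90% CI (one-sided 0.05, as in the sizing) is below +5 points. Report the relative ratio with its 95% CI as supportive, and state that P>0.05 for a difference is not evidence of equal efficacy. In the Study hypothesis section, state the null as an excess of 5 points or more with the single dose.

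Restate the power whichever interval decides, using the figures in step 5: neither rule reaches the planned 80% at the current size. Rewording alone therefore does not complete the repair; it has to be read together with a corrected sample size, which at the stated rates is 594 per group before dropout for the 90% CI rule.

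The rewording needs no new data. Its cost is that the stated power becomes less favourable and, at the present size and planning rates, an inconclusive result becomes more likely than not.

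### The trial is sized to reject a 5-point excess in infection risk, but the planned analysis tests for zero difference and compares no result with that margin

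*Protocol article*

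**What the plan says.** Three sections of the protocol article bear on this point.

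- **Study hypothesis.** The trial sets out from similarity: "there is no clinically significant difference between a single dose of gentamicin in combination with metronidazole and multiple doses over 24 hours".
- **Sample size estimation.** The number of women is derived from a margin: "If we assume the hypothesized difference, D to be 5%, the sample size needed to reject this hypothesis", "at alpha = 0.05 and beta = 0.20". The formula uses Z0.95 and Z0.80 and divides by (Ps − Pn − D)². The expected risks are given as "we use Ps = 8.1%, which is the proportion of participants in the single dose antibiotic prophylaxis group" and "Pn = 6.9%, which is proportion of participants in the multiple dose antibiotic prophylaxis". The result is 222 per group before dropout and 245 after it.
- **Data analysis.** The test is described as "Hypothesis testing will be done to determine if there is a significant difference in cumulative incidence of post-caesarian infection". The absolute difference in proportions is named as the measure of effectiveness. Cumulative incidence and a relative ratio are to be shown with 95% confidence intervals and a P-value. D is not mentioned.

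The words non-inferiority and equivalence do not appear in the article. The section on dissemination says that the findings will be used to write a protocol for antibiotic prophylaxis.

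**The concern.** The null hypothesis used for sizing (an excess of D) and the null hypothesis to be tested (no difference) are not the same. Under the first, rejection supports the single dose. Under the second, rejection shows that the regimens differ, so the trial's own hypothesis sits in the null, where no test can establish it. Changing the alpha level does not reconcile the two.

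The only outcome of the planned test that could agree with the hypothesis is a non-significant one, and low precision makes that outcome more likely. What is at stake is whether a result compatible with five or more extra infections per 100 women can be told apart from one that excludes such an excess, in a trial meant to shape hospital practice.

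**Working it through.** **Inputs** (Sample size estimation): Ps = 0.081, Pn = 0.069, D = 0.05, one-sided alpha 0.05 (Z0.95 = 1.645), power 80% (Z0.80 = 0.842), 222 per group (245 with dropout).

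**1. The plan's own figure.** The standard form of the formula is n per group = (Z0.95 + Z0.80)² [Ps(1 − Ps) + Pn(1 − Pn)] / (Ps − Pn − D)².

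- Variance term: 0.081 × 0.919 + 0.069 × 0.931 = 0.1387.
- (1.645 + 0.842)² = 6.183.
- Denominator: (0.012 − 0.05)² = 0.038² = 0.001444.
- n = 6.183 × 0.1387 / 0.001444 = 594 per group.

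The stated 222 is not reproduced. A denominator of (0.012 + 0.05)² = 0.062² gives 223.0, or 221.9 with Z rounded to 1.64 and 0.84, which suggests that the sign of the assumed difference was reversed. The bracket exactly as printed gives about 4,008. Whatever the arithmetic, the form is that of a one-sided test against a margin.

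**2. How the two tests behave.** The figures below come from exact binomial enumeration. The difference test is the pooled two-proportion z-test at two-sided 5%. The margin test asks whether the upper Wald limit for single minus multiple dose is below 5 points. The two-sided 5% level is an assumption, taken from the 95% intervals in the analysis section.

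| True risks (single v multiple), n per arm | Difference test non-significant | Margin test passes, 90% CI | Margin test passes, 95% CI |
|---|---|---|---|
| 11.9% v 6.9%, 222 | 56.0% | 5.4% | 2.8% |
| 11.9% v 6.9%, 245 | 52.5% | 5.4% | 2.8% |
| 8.1% v 6.9%, 222 | 92.5% | 45.9% | 33.9% |
| 8.1% v 6.9%, 245 | 92.1% | 48.9% | 37.0% |

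The 11.9% is Pn + D = 6.9% + 5 points, the excess that the trial is meant to reject.

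**3. Disagreement at the plan's own rates.** With 222 per arm, 47.4% of all trials are non-significant while the upper 90% limit is 5 points or more. With the 95% limit this is 59.3%.

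**4. Two examples with 222 per arm.**

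- 18 v 15 infections: difference 8.11% − 6.76% = 1.35 points, P = 0.59, 95% CI −3.5 to +6.2 points, upper 90% limit 5.4 points.
- 27 v 17 infections: difference 12.16% − 7.66% = 4.50 points, P = 0.11, 95% CI −1.0 to +10.0 points, upper 90% limit 9.2 points.

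Both are non-significant and neither excludes a 5-point excess. The second is compatible with twice that.

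**The case against.** **The decision rule is inferred.** A reader might conclude that the plan treats a non-significant P-value as proof that the single dose is as good. The article does not say so. The dissemination section says that the findings will be used, not which result leads to which regimen. This objection stands, and the point is limited accordingly: the planned test has no outcome that could establish the hypothesis, and no stated rule links the result to D.

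**The analysis is not P-value only.** It names the absolute difference, which is the scale of D, and promises confidence intervals. With the numbers in each arm, a reader could compute the limit and compare it with 5 points. This is a partial mitigation. As worded, the intervals belong to cumulative incidence and the relative ratio, and a limit on a ratio cannot be read directly against an absolute margin.

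**The rule may be in a fuller document.** An article condenses its protocol, so the absence of a margin rule would not by itself be a finding. What remains is what the article does state: a test of difference that conflicts with its own sizing.

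**Missed infections.** A reader might add that diluted or missed infections favour the wanted conclusion under the planned test. That does not separate the two analyses, because they push a margin test the same way. As an illustration, if only 70% of infections were detected in both arms (an assumption), true risks of 11.9% and 6.9% would appear as 8.33% and 4.83%, and the margin test (90% CI, 222 per arm) would wrongly pass in about 17% of trials instead of 5%. The argument is not used here.

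**Conclusion.** The contradiction is in the text and affects the primary conclusion. The planned test of zero difference does not match a trial sized against a 5-point margin. With a true 5-point excess, 222 per arm and a two-sided 5% test, the only result that could agree with the hypothesis occurs in 56% of trials (53% with 245 per arm), against about 5% for a test of the margin.

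These figures assume a multiple-dose risk of 6.9%, as the plan does. They do not rest on any claim that the investigators intend to read non-significance as success. Nor can it be said that the trial as sized would rule out a 5-point excess with 80% power: that is the intent of the formula, but the stated inputs need 594 per arm.

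**What to change.** In Data analysis, replace the sentence on hypothesis testing with wording to this effect:

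*The null hypothesis is that the risk of surgical site infection (single minus multiple dose) is higher by 5 percentage points or more. Non-inferiority of the single dose is declared only if the upper limit of the two-sided 90% confidence interval for this absolute difference is below 5 points. Any other result that does not show harm is inconclusive. The test for a difference is supportive, and a non-significant P-value is not evidence for the study hypothesis.*

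The 90% interval matches the one-sided 5% used for sizing. If the 95% interval is preferred, restate alpha in Sample size estimation as one-sided 0.025. The same inputs then need 754 per arm. The study hypothesis should be expressed as the alternative to this null.

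The wording itself changes no treatment and no data collection. Recruitment had already begun when the article was written, so the rule should be fixed before outcomes are compared by arm.

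The cost is that the trial may well be inconclusive. At 8.1% v 6.9% with 222 per arm, the margin test succeeds in about 46% of trials (34% with the 95% interval). The sample-size error needs its own correction, and the power should be restated with this change.

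### The trial is sized on an absolute 5-point difference, but the analysis plans its comparative interval for a ratio and never compares anything with 5 points

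*Protocol article*

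**What the plan says.** Three statements in the protocol article bear on this point.

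- **Sample size estimation.** The wording is "If we assume the hypothesized difference, D to be 5" (per cent), and the sample size is the number needed to reject that hypothesis "at alpha = 0.05 and beta = 0.20". D is subtracted from Ps − Pn in the denominator of the formula, so it is in absolute percentage points. The result is that "the required sample size in each group will be 222".
- **Data analysis, effect measure.** The section states: "The absolute difference in the proportion of women who will develop surgical site infection in the two study arms will be the effectiveness". The abstract says the same.
- **Data analysis, reporting and testing.** "Results will be presented in cumulative incidence and as a relative ratio together with 95% confidence intervals", with a P-value. The hypothesis test asks whether the cumulative incidences of the two arms differ significantly.

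The study hypothesis is that the two regimens do not differ by a clinically meaningful amount. The 5% in the sample size section is the only figure that gives this a size.

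**The concern.** The sizing and the named effect are both on the absolute scale. The only comparative interval expressly planned is on the relative scale, and the only test expressly planned is against no difference. Neither answers the question for which the trial was sized, namely whether an excess of 5 points can be ruled out.

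A non-significant test does not show that two regimens are similar. If it is read as support for the hypothesis, the trial could conclude that a single dose is as good while its own data remain compatible with more than 5 extra infections per 100 women. According to the section on dissemination, the findings will be used to write the hospital's prophylaxis protocol, so such a conclusion would have direct consequences.

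**Working it through.** **Inputs** (Sample size estimation): Ps = 8.1% (single dose), Pn = 6.9% (multiple dose), D = 5 points, Z0.95 and Z0.80, 222 per arm, background incidence 2.5% to 20%.

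**1. The plan's own figure.** The usual absolute-scale formula is (Z0.95 + Z0.80)² × [Ps(1−Ps) + Pn(1−Pn)] / (Ps − Pn − D)².
- (Z0.95 + Z0.80)² = 6.183. The variance term is 0.0744 + 0.0642 = 0.1387.
- With the printed sign, 6.183 × 0.1387 / 0.038² = 594 per arm.
- With the sign of D reversed, 6.183 × 0.1387 / 0.062² = 223 per arm, close to the stated 222.

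The stated size therefore reproduces only with D reversed. That is a separate matter. What counts here is that the formula works on the absolute scale in either case, with a one-sided 5% level (Z0.95). A one-sided 5% level corresponds to a 90% two-sided interval.

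**2. What 5 points means as a ratio.** At multiple-dose risk p, the equivalent ratio is (p + 0.05)/p.
- p = 2.5%: 0.075/0.025 = 3.0
- p = 6.9%: 0.119/0.069 = 1.72
- p = 20%: 0.25/0.20 = 1.25

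Over the protocol's own range of incidence, the same 5 points moves from a trebling to a quarter more. A ratio interval alone cannot show on which side of 5 points the data lie. An interval for each arm's incidence is not an interval for their difference either.

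**3. An example that needs no ratio limit.** Take 222 per arm with 18 (8.1%) versus 15 (6.8%) infections, close to the planned rates.
- Ratio: 18/15 = 1.20. The standard error of the log ratio is √(1/18 − 1/222 + 1/15 − 1/222) = 0.336. The 95% CI is 1.20 × exp(±1.96 × 0.336) = 0.62 to 2.32. A pooled two-proportion test gives z = 0.54, P = 0.59. Under the planned test, the arms do not differ significantly.
- Difference: 8.11 − 6.76 = +1.35 points. The 95% Wilson limits are 5.19 to 12.45 (single) and 4.14 to 10.85 (multiple). The Newcombe upper limit is 1.35 + √[(12.45 − 8.11)² + (6.76 − 4.14)²] = 6.4, and the lower limit is −3.7. At 90% the upper limit is 5.6.

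Five points is not excluded at either level, although the planned outputs would read as no significant difference.

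**4. The planned rates themselves.** The standard error of the difference is √(0.1387/222) = 2.50 points. The upper limit is 1.2 + 1.96 × 2.50 = 6.1 (95%) or 1.2 + 1.645 × 2.50 = 5.3 (90%). Both exceed 5. The ratio at the same rates is 1.17 (95% CI 0.61 to 2.26).

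**The case against.** Several points on the other side have weight.

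- **The sentence can be read more generously.** It follows directly on the one that names the absolute difference, and a reader may take the intervals to cover results in general. This is a condensed article and the full protocol is not shown. A reader might infer that the trial will report its main effect with no interval at all, but the text does not say so. What stands is narrower: the intervals are expressly tied to incidence and a ratio, none is expressly tied to the difference, and nothing is compared with 5 points.
- **D is not called a margin.** The article calls it a hypothesised difference and never uses the term non-inferiority. Its role as a limit is inferred from the formula, the statement that it is to be rejected and the study hypothesis. The inference is sound, but it is an inference.
- **The two scales need not give opposite verdicts.** A reader might infer that the ratio interval would reverse the absolute verdict in a large share of trials. The protocol does not support this, because it sets no limit on the ratio. Such claims need an assumed ratio limit, for example 1.72 from converting 5 points at 6.9%. Applying that limit where the risk is 2.5% or 20% builds in much of the disagreement. The example of 18 versus 15 avoids this assumption.
- **No data are lost.** Anyone with the arm counts can rebuild the interval for the difference. That limits the seriousness of the point but does not settle in advance which quantity decides.

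The choice of interval method is ordinary analysis-plan detail, and its absence is not part of this point.

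**Conclusion.** The point holds as a mismatch between elements that the article itself states. The sizing and the effect measure are absolute; the expressly planned comparative interval is relative; and the test is against no difference. As written, the analysis never judges the 5 points. Near the planned rates with 222 per arm, it would report no significant difference while the upper limit for the excess is 6.4 points (95%) or 5.6 (90%).

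This rests on reading D as the limit to be excluded and on 222 evaluable women per arm. It does not rest on any ratio limit. It should be corrected, but it is a fault in the planned basis for the conclusion and does not damage the data.

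**What to change.** In Data analysis, make the primary result the absolute difference in proportions, single minus multiple, with its own confidence interval by a method suited to low event counts (for example Newcombe or Miettinen-Nurminen). Base the conclusion on whether the upper limit is below 5 points, in place of the test for a significant difference. State the confidence level and reconcile it with the sample size section: Z0.95 corresponds to a 90% two-sided interval, and if 95% is kept, say that this is stricter than the sizing. Call the relative measure a risk ratio and report it as supportive only.

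This takes a few sentences and a few lines of code, with no new data. There is a small downside, in that a claim of no clinically meaningful difference becomes harder to make. At the planned variance with 222 per arm, the half-width is 4.1 points (90%) or 4.9 (95%). The observed excess would have to be below about 5 − 4.1 = 0.9 or 5 − 4.9 = 0.1 points, whereas the plan expects 1.2.
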